## Abstract

**Background:**

The Rho-kinase (ROCK) inhibitor Fasudil has shown symptomatic and disease-modifying effects in Parkinson’s disease (PD) models *in vitro* and *in vivo*. In Japan, Fasudil has been approved for the treatment of subarachnoid haemorrhage since 1995 and shows a favourable safety profile.

**Objectives/design:**

To investigate the safety, tolerability, and symptomatic efficacy of ROCK-inhibitor Fasudil in comparison to placebo in a randomized, national, multicenter, double-blind phase IIa study in patients with PD.

**Methods/analysis:**

We plan to include 75 patients with at least ‘probable’ PD (MDS criteria), Hoehn and Yahr stages 1–3, and age 30–80 years in 13 German study sites. Patients must be non-fluctuating and their response to PD medication must have been stable for 6 weeks. Patients will be randomly allocated to treatment with the oral investigational medicinal product (IMP) containing either Fasudil in two dosages, or placebo, for a total of 22 days. As primary analysis, non-inferiority of low/high dose of Fasudil on the combined endpoint consisting of occurrence of intolerance and/or treatment-related serious adverse events (SAEs) over 22 days will be assessed in a sequential order, starting with the lower dose. Secondary endpoints will include tolerability alone over 22 days and occurrence of treatment-related SAEs (SARs) over 22 and 50 days and will be compared on group level. Additional secondary endpoints include efficacy on motor and non-motor symptoms, measured on established scales, and will be assessed at several timepoints. Biomaterial will be collected to determine pharmacokinetics of Fasudil and its active metabolite, and to evaluate biomarkers of neurodegeneration.

**Ethics/registration/discussion:**

After positive evaluation by the competent authority and the ethics committee, patient recruitment started in the 3rd quarter of 2023. ROCK-PD is registered with Eudra-CT (2021-003879-34) and clinicaltrials.gov (NCT05931575). Results of this trial can pave way for conducting extended-duration studies assessing both symptomatic efficacy and disease-modifying properties of Fasudil.

## Introduction

1

Parkinson’s disease (PD) is a progressive neurodegenerative disorder with a multi-factorial pathogenesis. Multiple molecular pathways, such as dysfunction in the ubiquitin-proteasome system, defective lysosomal degradation and autophagy, protein aggregation, mitochondrial malfunction, and oxidative stress, have been implicated as disease mechanisms (Obeso et al., 2017; Burré et al., 2018). Up to now, only symptomatic treatments are available and there is a great need to develop disease-modifying therapies (Stocchi and Olanow, 2013). Because of the multifactorial pathogenesis of PD, disease-modifying treatments will also have to address multiple mechanisms. Fasudil is a small-molecule inhibitor of Rho-associated coiled coil kinase (ROCK), an enzyme that is known to mediate vasoconstriction and vascular remodelling by regulation of the actin cytoskeleton. Interestingly, inhibition of ROCK was also demonstrated to increase actin fluidity and thus regenerative capacity in neuronal growth cones, to activate cell survival and protein synthesis pathways (via Akt, PTEN, and mTOR) (Li et al., 2005; Park et al., 2011), as well as to modulate microglial function by changing the microglial phenotype from the rather cytotoxic M1 to the rather cytoprotective M2 (Zhang et al., 2013). ROCK expression is increased in several neurodegenerative disorders, including Amyotrophic lateral sclerosis (ALS), Alzheimer’s disease, and PD (Koch et al., 2018). The ROCK-inhibitor Fasudil was originally developed as a vasodilatory drug and was licensed in Japan in 1995 for the treatment of vasospasms following subarachnoid haemorrhage (SAH). It has been tested in numerous clinical trials since, most frequently for cardiovascular diseases (Ruan et al., 2019; Hou et al., 2022). Fasudil is primarily metabolized in the liver, resulting in the formation of its active metabolite, Hydroxyfasudil, subsequently undergoing renal excretion. Clinical meaningful quantities of Hydroxyfasudil also cross the blood–brain barrier (Taniguchi et al., 2014). This makes Fasudil a potential candidate for the treatment of central nervous system disorders. The effects of Fasudil were assessed in a phase 3 trial in patients with acute ischemic stroke, where Fasudil treatment significantly improved clinical outcome (Shibuya et al., 2005). Additionally, beneficial effects on survival and motor function have been observed in animal models of ALS (Takata et al., 2013; Tönges et al., 2014; Günther et al., 2017) and other neurodegenerative disorders, e.g., Alzheimer’s disease (Koch et al., 2018). Currently, an investigator-initiated, international multicenter trial is ongoing to evaluate safety, tolerability, and efficacy of Fasudil in patients with ALS (ROCK-ALS, NCT03792490, Eudra-CT: 2017-003676-31)^1^ (Lingor et al., 2019). We and others demonstrated that Fasudil exerts neuroprotective and pro-regenerative effects in PD models *in vitro* and *in vivo*: Fasudil protected dopaminergic tyrosine hydroxylase-positive nigral neurons from degeneration, increased their regeneration and resulted in increased striatal dopamine levels accompanied by a behavioural improvement in rodents (Tönges et al., 2012; He et al., 2016; Yang et al., 2020). Importantly, Fasudil specifically binds to alpha-synuclein at two tyrosine residues (Y133 and Y136) and attenuates aggregation of alpha-synuclein *in vitro* and *in vivo*, independently from its effects on the actin cytoskeleton (Tatenhorst et al., 2016). Furthermore, Fasudil has shown symptomatic efficacy by dopaminergic effects (Sortwell et al., 2013) and reduction of L-Dopa-induced dyskinesia (Lopez-Lopez et al., 2020) in preclinical rodent models, suggesting that it could also be beneficial for patients in the short term. Taken together, Fasudil has shown multiple disease-modifying properties in models of PD *in vitro* and *in vivo* making it a highly promising candidate for disease-modifying therapeutic trials in PD (Tönges et al., 2012; Tatenhorst et al., 2014, 2016; Koch et al., 2018). An intravenous formulation of Fasudil is licensed in Japan, oral (tablet) formulations, including extended release formulations, were previously used in clinical trials in humans (Vicari et al., 2005; Fukumoto et al., 2013) and a good enteric bioavailability of the drug has been documented (Hinderling et al., 2007). The longest published exposure to Fasudil in humans was 8 and 12 weeks (angina pectoris and pulmonary arterial hypertension) (Vicari et al., 2005; Fukumoto et al., 2013). Side effects included allergic skin reactions, a mild drop in systolic blood pressure, and reversible renal impairment without major safety concerns. In view of the ample preexisting clinical experience with Fasudil and its well-known safety profile (Suzuki et al., 2007, 2008) it represents an excellent candidate for repositioning as a disease-modifying therapy in PD (Koch et al., 2018).

We present here the design of a randomized, placebo-controlled, national, multicenter, double-blind phase IIa study for safety, tolerability, and symptomatic efficacy of the ROCK-inhibitor Fasudil in patients with PD. So far, ROCK-inhibition has not yet been evaluated in the treatment of PD making this trial unique. Considering the potential symptomatic and disease-modifying effects of Fasudil in PD, patients could benefit from attenuation of disease-progression as well as from immediate clinical improvement.

## Methods and analysis

2

### Objectives and design

2.1

The objective of the ROCK-PD trial is to establish a safety and tolerability profile of the ROCK-inhibitor Fasudil by testing for non-inferiority against placebo, and asses symptomatic efficacy in patients with PD. It is designed as a multi-center, prospective, interventional, randomized, double-blind, placebo-controlled, parallel-group, phase IIa trial. In brief, patients with PD, who are non-fluctuating on their antiparkinsonian medication, will be recruited to receive either Fasudil in two dosages, or placebo, over a period of 22 days. Two follow-up visits (until day 50) will establish safety and symptomatic effects during wash-out (Figure 1). The SPIRIT guidelines were followed in the preparation of the trial protocol (Chan et al., 2013; Supplementary Table S1) and study results will be published in accordance with the CONSORT guidelines (Moher et al., 2010).

**Figure 1 fig1:**
[figure not shown]
Visit schedule of the ROCK-PD study *IMP (investigational medicinal product either containing Fasudil [44 mg or 22 mg] or placebo) administration at day 1 and day 22 once daily, on days 2–21 twice daily.

### Participants

2.2

#### Inclusion and exclusion criteria

2.2.1

Patients with a diagnosis of at least ‘probable’ PD according to MDS criteria (Postuma et al., 2015), and a Hoehn and Yahr stage 1–3, aged 30 to 80 years are eligible for participation in the ROCK-PD trial. Furthermore, patients must be non-fluctuating (no wearing-off, no dyskinesia) and stable on symptomatic PD medication for at least 6 weeks before screening and baseline. Atypical, secondary parkinsonian syndromes, or any other medical condition known to have an association with parkinsonian syndromes, which might confound or obscure the diagnosis of PD are excluded. Other main exclusion criteria are a history of intracranial bleeding, known intracerebral aneurysms, or Moyamoya disease (due to the Fasudil label). In case of a positive family history for the aforementioned conditions, MR- or X-ray-based imaging not older than 24 months must confirm their absence. Patients with drug-treated pulmonary hypertension, drug-treated arterial hypotension, or unstable or uncontrollable arterial hypertension are also excluded from the trial. Conditions interfering with the safety measurements of this trial, such as confirmed hepatic or renal insufficiency are additional exclusion criteria. The full list of inclusion and exclusion criteria is provided in Table 1.

**Table 1 tab1:** Inclusion and exclusion criteria of the ROCK-PD trial.

*Inclusion criteria*
Patients with a diagnosis of at least ‘probable’ PD according to MDS criteria (Postuma et al., 2015). Hoehn and Yahr stage 1–3. must be non-fluctuating (no wearing-off, no dyskinesia) and stable on symptomatic PD medication for at least 6 weeks. Age: 30–80 years. Women of childbearing age must be non-lactating and surgically sterile or using a highly effective method of birth control and have a negative pregnancy test. Acceptable methods of birth control with a low failure rate (i.e., <1% per year) when used consistently and correct are for example implants, injectables, combined oral contraceptives, hormonal intrauterine devices (IUDs), sexual abstinence, or vasectomized partner. Capable of thoroughly understanding all information given and giving full informed consent according to GCP.
*Exclusion criteria*
Atypical, secondary Parkinsonian syndromes, PD mimics, or any other medical condition known to have an association with Parkinsonian syndromes, which might confound or obscure the diagnosis of PD. Patients with a history of intracranial bleeding, known intracerebral aneurysms or Moyamoya disease, or positive family history for the above. If family history positive, MR- or x-ray-based cranial imaging not older than 24 months must confirm absence of bleeding, aneurysms, or Moyamoya disease. Presence of any concomitant life-threatening disease or impairment likely to interfere with functional assessment. Patients with known arterial hypotension (resting blood pressure <90/60 mmHg), previous hypotensive episodes, or requiring treatment, such as fludrocortisone, midodrine, etilefrine, cafedrine, or theodrenaline. Patients with an uncontrollable or unstable arterial hypertension (resting blood pressure >180 mmHg systolic and/or >120 mmHg diastolic, whether or not under current antihypertensive medication). Known pulmonary hypertension and any medication prescribed for treatment of pulmonary hypertension. Confirmed hepatic insufficiency or abnormal liver function (stable ASAT and/or ALAT >3 times the upper limit of the normal range) and determined to be non-transient through repeat testing. Renal insufficiency with a glomerular filtration rate (GFR) <60 mL/min/1,73 m^2^ (calculated by MDRD equation) and determined to be non-transient through repeat testing. Major psychiatric disorder, significant cognitive impairment or clinically evident dementia precluding evaluation of symptoms. Hypersensitivity to any component of the IMP. Liable to be not cooperative or comply with the trial requirements (as assessed by the investigator), or unable to be reached in the case of emergency. Pregnant or breast-feeding females or females with childbearing potential, if no adequate contraceptive measures are used. Previous participation in another clinical study involving trial medication within the preceding 12 weeks or five terminal half times of the longest to be eliminated trial medication (whichever is longer) or previous participation in this trial.

#### Recruitment

2.2.2

Patients will be recruited and assessed for eligibility at currently 13 study sites in Germany. All study sites are part of the German competence network for Parkinson’s disease (accessed on March 15, 2023)^2^ and are actively involved in the treatment of several hundred PD patients per year. A web site has been established to inform referring centers about the trial (accessed on September 27, 2023).^3^ All patient assessments including the screening visit will be performed at the study sites. Recruitment started in the 3rd quarter 2023 and is anticipated to be completed by the 3rd quarter 2024. Throughout the clinical trial, recruitment rates will be monitored for each study site.

### Randomization and blinding

2.3

Participants will be randomized into three parallel groups at an allocation ratio of 1:1:1 (Figure 1). There will be two Fasudil treatment arms (low and high dosage) and one placebo arm. Allocation will be performed based on a computer-generated randomization list. All procedures will be performed double-blind (patient- and investigator blind). During the clinical trial, unblinding may only occur in the case of an emergency, where the choice of treatment depends on the study subject’s therapy assignment. Emergency envelopes for the unblinding of study participants are provided.

### Drug procurement and intervention

2.4

Fasudil hydrochloride hydrate (Eril 30 mg, 15 mg/mL ampoules) has been imported from Asahi Kasei Pharma Corporation, Tokyo, Japan, by a licensed importer and provided to the central pharmacy for this clinical trial (Pharmacy at University of Leipzig Medical Center, Germany), where it will be decanted and blinded as IMP (22 or 44 mg, 15 mg/mL stock solution). Due to the bitter taste of Fasudil, the placebo formulation requires the addition of a bittering agent. As a bittering agent, Quinine dihydrochloride solution (Quinina Labesfal 500 mg, 250 mg/mL ampoules) has been imported from Labesfal – Laboratórios Almiro, Santiago de Besteiros, Portugal, by a licensed importer and provided to the central pharmacy where it will be re-packaged as IMP (12.5 mg, 250 mg/mL stock solution). The IMP will be produced, packaged, stored, blinded, labelled, and shipped to the trial sites in accordance with the legal requirements and good manufacturing practice. Participants will orally administer the IMP every 12 h, with a tolerance window of ±1 h. Before oral self-administration, participants will supplement the IMP with 30 mL Glucose 40% solution.

### Study procedures

2.5

A total of six visits (V0-V5) will be performed (see Table 2). Informed consent will be obtained before any study-specific procedure. During the screening visit (V0), eligibility according to inclusion and exclusion criteria, medical history, vital signs, concomitant medication, height, and weight will be established. A physical examination will be complemented by assessment of modified Hoehn and Yahr scale (mHY) and laboratory tests for safety parameters. This visit may take place up to 42 days in advance to the start of the treatment period. At the beginning of the treatment period, a baseline visit will be performed (V1). At this stage, we will reconfirm the inclusion and exclusion criteria, assess baseline measurements of laboratory parameters, vital safety indicators, and symptom-related assessment scales. These scales include the MDS-Unified PD Rating Scale I-IV (MDS-UPDRS), PD Quality of Life Scale (PDQ-8), PD Non-Motor Symptom Questionnaire (NMSQuest), Montreal Cognitive Assessment (MoCA), Beck’s Depression Inventory-II (BDI-II), and Global Impression of Improvement score (CGI-I [clinician], PGI-I [patient]). Participants will start intake of IMP in the evening after V1 and continue for 22 days. On the morning of day 22 the last dose should be administered at the study site. Safety parameters (laboratory measures and vital signs) will be assessed at all study related visits. These are on day 10 (±2 days; V2) and day 22 (−2 days; V3), during the treatment period, as well as day 36 (±3 days; V4) and 50 (±3 days; V5) during the washout period. At visits V2 and V3, tolerability will be recorded. Symptomatic efficacy will be assessed during treatment period (V2: subset of scales: MDS-UPDRS, subscales III and IV, NMSQuest, PGI-I, CGI-I), on the last day of treatment (V3), and after the wash-out phase (V5). We will collect biomaterials, including blood, cerebrospinal fluid (CSF), and tear fluid, for the purpose of establishing the pharmacokinetics of oral Fasudil and its active metabolite, Hydroxyfasudil. Additionally, these samples will be used to measure target engagement (ROCK activity) and for biobanking.

**Table 2 tab2:** Trial visit schedule.

Visit item	V0 screening	V1 BL	V2	V3	V4	V5
Day (d)	0	1	10	22	36	50
Permitted delta in days (±) to V1	−42	0	±2	−2	±3	±3
IMP orally 2x/d, on day 1 and day 22 1x/d		x	x	x		
*Screening assessment/randomization*						
Patient information and informed consent	X					
Inclusion/exclusion criteria	X	X				
Demographics	X					
Medical history	X					
Diagnosis according to MDS criteria	X					
Modified Hoehn and Yahr scale (mHY)	X					
Physical examination	X					
Randomization	X^*^					
*Recurrent additional status data*						
Concomitant treatment history	X	X	X	X	X	X
Vital signs (pulse, BP)	X	X	X	X	X	X
Height (only at screening), weight	X	X		X		X
*Endpoint assessment*						
Adverse events/tolerability (acquisition only after first drug intake)		X	X	X	X	X
MDS-UPDRS, subscales I and II^**^		X		X		X
MDS-UPDRS, subscales III and IV^**^		X	X	X		X
NMSQuest		X	X	X		X
MoCA^***^		X		X		X
BDI-II		X		X		X
PDQ-8		X		X		X
PGI-I (patient) and CGI-I (health professional)			X	X		X
*Laboratory assessments*						
Safety parameters^****^	X	X	X	X^§^	X	X
Pregnancy test (if female and fertile)	X	X	X	X	X	X
*Samples for exploratory analyses and biobanking*						
Fasudil/Hydroxyfasudil in CSF and plasma		P		C^#^&P^#^		P
ROCK activity in plasma		X		X		X
*Additional samples for biobanking (separate ICF)*						
Serum/plasma/tear fluid		X		X		X
EDTA blood		X				
CSF				X		

^*^Randomization takes place between V0 and V1 by central pharmacy. ^**^MDS-UPDRS assessment has to be performed at the same interval to IMP intake in each patient (±1 h). ^***^Different versions of MoCA will be used at each assessment. ^****^RBC, WBC, PLT, creatinine, GFR (MDRD), ALAT, ASAT, GGT, and CK. ^§^Additional parameters: INR, PTT. ^#^Sample collection has to be performed 120 ± 60 min after the intake of last trial medication.

#### Harmonisation of cohorts and methods

2.5.1

ROCK-PD exclusively enlists academic hospitals known for their expertise in conducting PD clinical trials. Clinical assessments employ established scales to evaluate PD features, administered by trained personnel at all participating centers. Although training certificates are not mandatory, the consistent expertise of these teams ensures the accuracy of clinical evaluations. Conducting the laboratory work-up is entrusted to trained personnel following rigorous protocols. A detailed biomaterial protocol has been prepared, providing a transparent account of the processes involved in handling and analysing biomaterials. Oversight is maintained by a monitoring board, conducting regular virtual and on-site visits. This proactive monitoring ensures protocol adherence and data integrity, instilling confidence in the reliability of the collected data.

### Outcomes

2.6

#### Primary outcome

2.6.1

The composite primary endpoint consists of the occurrence of intolerance, defined as termination of treatment because of treatment-related adverse effects (AE), and/or self-reported or pre-defined (laboratory, vital signs) treatment-related serious adverse effects (SAE) from day 1 (V1) to day 22 (V3) of the treatment period.

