#### Secondary outcomes

2.6.2

The occurrence of intolerance (termination of treatment because of treatment-related AE; time frame: from V1 to V3) and the occurrence of self-reported and pre-defined (laboratory, vital signs) treatment-related SAEs (from V1 to V3 and V1 to V5) will be assessed alone as two separate secondary outcomes. Furthermore, the symptomatic efficacy of oral Fasudil will be assessed as change of MDS-UPDRS (part I to IV from V1 to V3 and V1 to V5; part I and II from V1 to V3 and V1 to V5; part III and IV from V1 to V2, V1 to V3, and V1 to V5), the change of PDQ-8 (from V1 to V3 and V1 to V5), the change of NMSQuest (from V1 to V2, V1 to V3, and V1 to V5), the change of MoCA (from V1 to V3 and V1 to V5), the change of BDI-II (from V1 to V3 and V1 to V5), and the CGI-I/PGI-I (at V2, V3, and V5).

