### Safety

2.7

The clinical trial will be monitored by an independent Safety Monitoring Board (SMB). The SMB will conduct regular safety reviews throughout the clinical trial to assess the progress of the trial. All adverse events (AE) will be collected from V1 (start of IMP intake). Each AE is to be classified by the investigator as “serious” or “non-serious.” This classification of the gravity of the event determines the reporting procedures to be followed. The intensity of AE will be graded using the Common Terminology Criteria for Adverse Events of the U.S. Department of Health and Human Services. All SAE will be subject to a second assessment by a medical expert, who will be independent from the sponsor. The second assessor will monitor for a relationship between SAE and IMP and expectedness of SAE (derived from reference safety information). All serious adverse reactions (SAR) will be determined a suspected unexpected serious adverse reaction (SUSAR) and require expedited reporting according to the applicable legal framework (competent authorities, ethic committees, clinical trial sites).

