### Sample size calculation

2.9

Expected probability for occurrence of the composite endpoint in the placebo arm is 5% at end of clinical trial. The two Fasudil arms are expected to reach about 12% each (according to the summary of product characteristics [SmPC] of Eril). A non-inferiority margin of 25% for the difference between Fasudil and placebo will be used based on data from previously published trials showing rates of discontinuation and severe adverse events of up to ~25% in patients treated with drugs that are in current clinical use for PD. For example, increased mortality was observed under selegiline/levodopa treatment (Lees, 1995), while side-effects (e.g., somnolence, dizziness, nausea) resulted in discontinuation in pramipexole-treated patients (Nissen et al., 2012; Schapira et al., 2013; Wang et al., 2017). Both drugs are in current use for PD. We thus consider a non-inferiority margin of ~25% as clinically and ethically acceptable for a drug that can have potentially disease-modifying properties and symptomatic effects. The two Fasudil arms will be tested against placebo in a hierarchical order, starting with the lower dose. This sequential procedure does not necessitate adjustment of the alpha level for multiple testing (Committee for Proprietary Medicinal Products (CPMP), 2002). According to the procedure no confirmatory claim can be based on the second test if the first test did not reach statistical significance. The significance levels are therefore each set to 10%, resulting to an overall type-I error of 10%. This error level was chosen in concordance with the recommendation of the European Medicines Agency (Committee for Medicinal Products for Human Use (CHMP), 2005). Given the aforementioned expected event rates, the non-inferiority margin and the alpha level of 10%, the sample size in each group needs to be 22 for a one-sided two-group test of proportions to reach a power of 80% to reject the null hypothesis that Fasudil is inferior to placebo in terms of its composite primary endpoint (calculated by nQuery Advisor V7.0, Statcon GmbH, Witzenhausen, Germany). A total of 3 × 25 = 75 patients are included in order to account for possible dropouts (for reasons other than intolerance; 12% drop-out).

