#### Primary endpoint analysis

2.10.2

The overall confirmatory significance level is set at 10%. The two primary hypotheses are that each Fasudil arm is non-inferior to the placebo arm referring to the composite primary endpoint. The two hypotheses are tested in a sequential order, first comparing arm B (=lower dose) against placebo and second comparing arm A (=higher dose) against placebo. A confirmatory claim can only be based on the second test if the first test did reach statistical significance. For each of the primary hypothesis tests, an exact one-sided 90% confidence interval (CI) of the differences (defined as placebo minus Fasudil) in the primary outcome will be computed to test non-inferiority. Statistical significance of non-inferiority is reached if the lower limit of the respective 90% CI is above the non-inferiority margin of −25%. Patients who leave the clinical trial prematurely due to reasons other than drug intolerance and treatment-related SAEs (e.g., refusal to come to follow-up visits, relocation to another city), will be excluded from the primary endpoint analysis.

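### Every listed safety outcome counts only events judged treatment-related, so even equal, blinded under-attribution narrows the difference tested against the fixed 25-point margin; an all-cause supplementary analysis should be pre-specified

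*Protocol article*

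**What the plan says.** Section 2.6.1 of the protocol article defines a two-part composite, intolerance and/or serious events, counted from V1 to V3: "termination of treatment because of treatment-related adverse effects (AE), and/or self-reported or pre-defined (laboratory, vital signs) treatment-related serious adverse effects (SAE"). The relatedness condition stands on both parts. Section 2.6.2 then lists the two parts as separate secondary outcomes under the same condition; the first reads "The occurrence of intolerance (termination of treatment because of treatment-related AE; time frame: from V1 to V3"). No outcome in 2.6 counts stops for an AE, or SAEs, whatever their attributed cause.

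Section 2.7 (Safety) adds one check on the causality judgement: "All SAE will be subject to a second assessment by a medical expert, who will be independent from the sponsor". No comparable check is stated for non-serious AEs that end treatment.

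Section 2.10.2 takes out of the primary analysis "Patients who leave the clinical trial prematurely due to reasons other than drug intolerance and treatment-related SAEs". Its examples are administrative, but as worded it also covers a patient who leaves because of an AE judged unrelated.

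Three provisions work the other way. Section 2.3 makes the trial patient- and investigator-blind. Section 2.7 states that "All adverse events (AE) will be collected from V1 (start of IMP intake"). Section 2.8 requires the reason for every premature termination to be assessed and documented in the eCRF.

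**The concern.** An event reaches the primary analysis only after a patient-level causality judgement, and that judgement is difficult here. Study medication is added to routine PD therapy (section 3.3). Section 2.9 itself recalls that "side-effects (e.g., somnolence, dizziness, nausea) resulted in discontinuation in pramipexole-treated patients". The Introduction lists a mild fall in systolic blood pressure among the side effects of Fasudil. Dizziness that ends treatment could therefore be put down to the study drug, to background medication or to PD itself.

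If some events caused by Fasudil are judged unrelated, both observed rates fall and so does their absolute difference. The margin stays at 25 points. In a superiority trial this dilution would work against the claim; in this non-inferiority comparison of harm it works for it. Randomisation against placebo already provides a causal contrast that needs no individual attribution, but no listed outcome uses it. At stake is whether a non-inferior result can be shown not to depend on how events were attributed.

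**Working it through.** **Inputs from the article.** Expected rates of 5% (placebo) and 12% (each Fasudil arm), margin 25 points, one-sided alpha 10%, power 80%, 22 per arm, 12% dropout, 75 in total (2.9). The test is an exact one-sided 90% interval (2.10.2).

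**Inputs assumed.** The share q of events judged related is 0.9, 0.8 or 0.7 and equal in both arms. The true rates lie exactly at the margin, 5% and 30%. The exact method is taken as an unconditional score test with size at most 10%. The article gives no attribution rate.

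**Step 1: the plan's own figure.** n = (z₀.₉₀ + z₀.₈₀)² × [0.12×0.88 + 0.05×0.95] / (0.25 − 0.07)² = (1.2816 + 0.8416)² × 0.1531 / 0.0324 = 21.3, so 22 per arm. Then 22 / 0.88 = 25 and 3 × 25 = 75. Both stated figures reproduce.

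**Step 2: direction.** If unattributed events count as non-events, the observed difference is q × (30 − 5): 22.5, 20.0 and 17.5 points at q = 0.9, 0.8 and 0.7. Conversely, the true difference that appears as 25 points is 25/q: 27.8, 31.3 and 35.7 points.

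**Step 3: patients stay in as non-events.** This applies to someone who stops study medication for an AE judged unrelated but remains in the trial. The observed rates are 30q% and 5q%. The chance of passing comes from full binomial enumeration.

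**Step 4: patients are excluded under 2.10.2.** This applies to someone who leaves the trial. Each rate p becomes qp / [1 − (1−q)p]. At q = 0.8 this gives 0.24/0.94 = 25.5% and 0.04/0.99 = 4.0%, a difference of 21.5 points. The number analysed per arm is 22 less a binomial number of exclusions, and the exact test is recomputed for each pair of arm sizes.

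| Share judged related | Chance of non-inferiority, counted as non-events | Chance of non-inferiority, excluded |
|---|---|---|
| 100% | 8.6% | 8.6% |
| 90% | 12.7% | 10.8% |
| 80% | 18.3% | 13.6% |
| 70% | 25.6% | 17.1% |

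With 25 per arm, the non-event column becomes 7.3%, 11.2%, 16.8% and 24.9%. A real trial would lie between the two columns, depending on how many patients stop study medication but stay in follow-up.

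**Step 5: power of an all-cause version.** Suppose 5% of patients in each arm have an unrelated event (an assumption). The planned rates become 1 − 0.95×0.95 = 9.75% and 1 − 0.88×0.95 = 16.4%. Exact power with 22 per arm falls from about 70% to about 64%. The 70% is for the exact test; the plan's 80% corresponds to the normal approximation of step 1.

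**The case against.** The case against is substantial. A drug-related tolerability endpoint is a legitimate choice, and the article uses it consistently. Supplementary analyses and all-cause AE tables usually belong in the SAP, which is not shown. Attribution is blinded, with a bittered placebo to protect the blind. Patients must be non-fluctuating and stable on PD medication for at least six weeks, and known hypotension or previous hypotensive episodes are excluded. A new symptom within 22 days is then harder to blame on an unchanged regimen. SAEs get an independent second look.

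Much of this stands, but it bears on the size of the effect and not on its direction. Blinding limits unequal attribution between the arms; the calculation already assumes equal attribution, and the dilution remains. The SAP argument does not dispose of the point, because the relatedness filter is part of the outcome set that the article itself fixes.

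A reader might infer that unattributed events are lost and that nobody could check. The documents do not support that: all AEs and all termination reasons are recorded, a safety board reviews the trial regularly, and the article does not say that all-cause results will be withheld. A reader might also take the percentages as the trial's type I error. They are not. For the endpoint as defined, the test keeps its size at or below 10%. The percentages describe what happens if the all-event difference is what matters, and if the true Fasudil rate is 30% where the plan expects 12%.

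**Conclusion.** The point holds as a weakness in the outcome set, not as an error that invalidates the primary analysis. All listed safety outcomes depend on a relatedness judgement, the judgement has a stated second check for SAEs only, and no listed outcome avoids it. Equal under-attribution pulls the difference towards zero and makes non-inferiority easier to declare.

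At a true difference of 25 points with 22 per arm, the chance of passing rises from 8.6% to between 10.8% and 12.7% if 90% of events are judged related, and to between 17.1% and 25.6% if 70% are. The upper figures treat every unattributed event as a non-event; the lower ones exclude all those patients under 2.10.2. The direction follows from the definitions. The size rests on the assumed attribution share and true rates. The documents give no evidence that attribution would differ between the arms or that under-attribution would reach 30%.

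**What to change.** Keep the primary endpoint, the margin and the 75 patients. In 2.6 and 2.10, pre-specify a supplementary analysis with the same interval method and the same 25-point margin. An event is termination of study medication because of any AE, or any SAE, from V1 to V3, regardless of attributed cause. Patients who leave the trial because of any AE stay in this analysis as events and are not excluded. State that the result will be reported beside any non-inferiority claim, as supportive evidence and not as a second confirmatory hurdle.

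The cost is wording only, since AEs, SAEs and termination reasons are already collected. The drawback is power: unrelated background events are added to both arms, and with an assumed 5% background rate exact power is about 64% against about 70%. Missing the margin in this analysis would therefore not by itself overturn the primary result. It should be read together with the estimated difference and the list of events judged unrelated.
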